### Data management

Benchmarking assessments (as described in Table 1) are completed through use of an App (Store Scout App, managed by Monash University), a web portal (Aboriginal and Torres Strait Islander Healthy Diets ASAP, managed by University of Queensland) and purpose-built REDCap e-surveys (i.e., Policy Action Progress Audit, Environment Scan, resource-use surveys managed by Monash University and available on request). Trained assessors can access coaching in use of the data collection tools. Data stored on the Store Scout App and the Healthy Diets ASAP web-portal are protected with a designated user-ID and password. Users can view and edit the data they collect only.

REDCap survey data are available to specified users only with multi-factor authentication login. Individual survey links are sent to specific respondents via email with those respondents only able to view, enter and edit their own individual survey data.

Sales data are sent electronically from each of the stores, or from the store group (where relevant) to Monash University via email attachment or a password protected secure transfer file (as chosen by stores).

All data are kept secure at Monash University in a password protected directory, a shared Google drive, and in the Benchmarking for Healthy Stores database purposely designed for the study. All have designated user restrictions.

### Analysis and statistical methods

The data source for analysis of the primary outcome and some secondary outcomes is weekly sales reports provided by the stores. Unique store products are linked, using rule-based algorithms, machine learning and human verification, to nutrient data derived from the Australian Food, Supplement, and Nutrient Database, with discretionary food flagged from the Discretionary Food List developed by the Australian Bureau of Statistics [74, 75]. We use built-in, reliable data checking processes developed over the last decade in our research to assess and quantify the nutritional impact of sales.

Following data aggregation, the outcomes will be log-transformed. The main analysis for an outcome will be a simple ANCOVA analysis using sales data from July to December 2021 and 2023, and randomisation group for the primary outcome.

We anticipate that the impact of the intervention will be both immediate and gradual. In stores that receive the benchmarking intervention, we estimate an immediate 3.5% reduction in free sugars to energy purchased as a result of food retail practice change. A reduction in free sugars to energy at this level from the baseline shown in the Healthy Stores 2020 trial has been shown to be the equivalent to an approximate 10% lower risk for cardiovascular disease mortality [4]. We then expect a more gradual effect at the broader remote store level post-intervention as the benchmarking model is scaled up into policy and practice by different jurisdictions for the benefit of all remote communities, if found to be adoptable and effective.

Implementation fidelity will be assessed according to i) proportion of partner organisation representatives completing training; and, ii) annual benchmarking cycles fully completed in specified timeframes. Data will be collected on action plans and the resource input to their implementation.

Change in store best-practice policy action adoption and practice implementation with time will be described and used to interpret results of primary and secondary outcomes. Food price and Environment Scan survey results will be described for context.

Policy Action Assessment: Proportion of policy actions by adoption status (fully adopted, partially adopted, getting started, not yet started) for 2022, 2023 and 2024 for each intervention store will be calculated and any differences with time described.

Practice assessment: An overall score out of 100 is derived automatically by the Store Scout App following each store assessment in 2022, 2023 and 2024 in addition to a score out of 100 for each food/drink category. Differences in total and category scores with time for intervention stores and between intervention and control stores will be described.

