## Methods

This is a store-level pragmatic randomised parallel group, 2-arm, superiority trial with a 1:1 allocation. The study commenced in 2022.

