#### Sample size

There are 53 eligible stores in 45 communities across the NT serviced by the partner s. We anticipate from previous trials an 85% consent rate and no withdrawals (or loss to follow up for the primary outcome). A sample of 36 communities will have 90% power to detect an ~ 3.5% lower percentage change in the primary outcome, free sugars g/MJ (SD of % change = 3%). The mean effect size of an ~ 3.5% reduction in free sugars (g/MJ) is based on our Healthy Stores 2020 trial [4]. We commenced recruitment in 2022 and recruited 32 stores (Fig. 1 and Additional Table 1).

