## Methods: assignment of interventions (for controlled trials)

### Allocation

Computer generated random numbers were used to allocate stores in near equal numbers to intervention/control within the store group serviced by each partner organisation (i.e., ALPA, NT Health (Central Australia), NT Health (Top-End), Katherine West, Miwatj, Outback Stores). Two stores with ALPA and two stores serviced by Miwatj were forced as each of these store pairs were in the same community and so 15 stores were allocated to intervention and 17 to control. Allocation occurred simultaneously after the required sample of stores was reached.

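### Stores were randomised within six partner store groups, but the main ANCOVA has only baseline and arm; if partner group predicts the outcome, precision is lost, and the fix must also cover the forced same-community pairs

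*Protocol article*

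**What the plan says.** Under Allocation, the article states: "Computer generated random numbers were used to allocate stores in near equal numbers to intervention/control within the store group serviced by each partner organisation". It lists six groups: "ALPA, NT Health (Central Australia), NT Health (Top-End), Katherine West, Miwatj, Outback Stores". For two pairs of stores, one pair with ALPA and one serviced by Miwatj, allocation was forced because the two stores of each pair share a community. The result was 15 intervention and 17 control stores. The text does not say which arm either pair went to.

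Under Analysis and statistical methods, outcomes are log-transformed and the main analysis "will be a simple ANCOVA analysis using sales data from July to December 2021 and 2023, and randomisation group for the primary outcome". The inputs are therefore the 2021 value, the 2023 value and the arm. No partner or store-group term, and no term for shared community, appears in the article.

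Under Sample size, "A sample of 36 communities will have 90% power to detect an ~ 3.5% lower percentage change in the primary outcome", with an SD of percentage change of 3%; 32 stores were recruited.

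**The concern.** Balancing the arms within partner group means that differences between groups largely cancel in the treatment comparison. A model without the groups does not know this. It treats between-group variation as noise, so the reported standard error exceeds the real sampling error, the interval is too wide and the test rejects too rarely.

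It is plausible that partner group matters. The article says that ALPA and Outback Stores nutritionists are directly engaged in store operations and policy. Practitioners in health services and government cover several communities, sometimes in dual roles. NT Health is split by region for allocation. The team also chose partner as the factor to balance on. What is at stake is precision in a trial of 32 stores, not the validity of the estimate.

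**Working it through.** **Inputs.** From the article: effect 3.5%, SD 3%, six strata, 15 v 17 stores, no loss to follow-up. Assumed: two-sided alpha of 5% (not stated); residual SD of the ANCOVA equal to the 3% quoted for percentage change; stratum sizes (the flow diagram and additional table are not shown); and rho, the share of residual variance lying between partner groups, varied because no figure is given.

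**1. The plan's own figure.** n per arm = 2(1.960 + 1.282)² × 3² / 3.5² = 15.4, so 16 per arm and 32 in total. The exact t-test needs 17 per arm, 34 in total. At 36, power is 93.8% (normal) or 92.5% (t), so 36 for 90% is adequate. With 15 v 17 stores, the t-test power is 89.0%.

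**2. Why the standard error is too large.**
- Model SE without strata ≈ 3 × √(1/15 + 1/17) = 3 × 0.354 = 1.06, whatever rho is.
- True SE under stratified allocation ≈ 1.06 × √(1 − rho), which is 1.01, 0.95 and 0.89 at rho = 0.1, 0.2 and 0.3.

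These hand values assume perfect balance within strata, so they slightly overstate the gap. Simulation gives the realistic size.

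**3. Simulation, forced pairs left aside.** Layout A has strata of 3/3, 3/3, 2/3, 2/2, 2/3 and 3/3 (20,000 runs per scenario). Layout B has strata of 8, 5, 5, 4, 4 and 6 stores (6,000 runs for type I error, 4,000 for power). Both compare baseline + arm with the same model plus five stratum indicators (residual df 29 v 24).

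| rho | Type I without strata, A / B | Power without → with, A | Power without → with, B |
|---|---|---|---|
| 0 | 4.7% / 5.2% | 87.8 → 86.6% | 87.5 → 86.5% |
| 0.1 | 4.2% / 4.4% | 89.3 → 90.1% | 89.1 → 89.8% |
| 0.2 | 3.5% / 3.7% | 89.8 → 92.8% | 90.4 → 92.8% |
| 0.3 | 2.6% / 2.8% | 91.9 → 95.6% | 92.1 → 95.8% |

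In layout B, the model SE v the true SE without strata is 1.066 v 1.034 (+3%), 1.064 v 0.989 (+8%) and 1.050 v 0.901 (+17%) at rho 0.1, 0.2 and 0.3. In layout A the unstratified 95% interval is 3%, 9% and 15% wider than the stratified one (at rho 0.3, 4.29 / 3.72 = 1.15). With strata in the model, type I error stays near 5% in both layouts.

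**4. Cost if strata are useless.** In a t-test calculation, going from 29 to 24 df lowers power from 88.9% to 88.5%. Simulated, the loss is 1.0 to 1.2 points. In a deliberately uneven layout (5/6, 3/3, 3/3, 1/1, 0/2, 3/2), power without → with strata is 87.7 → 85.1% at rho 0, 89.6 → 88.6% at 0.1 and 90.2 → 91.4% at 0.2.

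**5. The forced pairs.** If both stores of a pair are in the same arm with within-pair correlation r, two pairs among 32 stores raise the variance of the contrast by roughly 4r/32. That is 6% at r = 0.5 (SE +3%) and 12.5% at r = 1 (SE +6%). Simulating layout A with one same-arm pair in each of two strata (12,000 runs) gives these type I errors, without / with strata:

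| rho | r = 0.5 | r = 0.9 |
|---|---|---|
| 0 | 5.6 / 5.8% | 6.5 / 6.7% |
| 0.1 | 4.6 / 5.7% | 5.0 / 6.4% |
| 0.2 | 4.0 / 6.0% | 4.3 / 6.5% |
| 0.3 | 3.1 / 5.7% | 3.8 / 7.3% |

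So the two omissions act in opposite directions, and repairing only the strata can move the test from conservative to slightly anti-conservative.

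**The case against.** The strongest reply is that a condensed article need not give the full covariate list and that a separate analysis plan may add the strata. That carries some weight, but the article does name the inputs of the main model and calls it simple, so the omission reads as a choice. Reading *randomisation group* as the stratum does not help, because the model would then have no treatment term.

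Second, the consequence is conditional. A reader might infer that the standard errors are certainly too large and the true type I error certainly below 5%. The documents do not support that. They report no between-partner variance, at rho = 0 the plan is right and adding strata costs power, and the forced pairs may offset a small stratum effect. This objection stands in full.

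Third, the effect on power is modest. A reader might infer that the omission leaves the trial underpowered, but in these simulations the stated model has about 88% to 92% power with 32 stores, close to the 90% target. In a very uneven layout the fix still loses about 1 point at rho = 0.1. That also stands.

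Fourth, differences in supply chain between partners are nowhere documented, and four of the six groups are named for a health service rather than a store operator. The case for partner as a predictor therefore rests on region, workforce and the two store groups.

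**Conclusion.** The mismatch between design and model is real: six strata in the allocation, none in the main ANCOVA. If partner group explains 10% to 30% of residual variance, and leaving the pairs aside, the stated model runs at a type I error of about 4% to 3%. Its interval is about 3% to 15% wider than it need be, and it gives up about 1 to 4 points of power. The treatment estimate is not biased, and false positives are not inflated by this omission. If partner group explains nothing, there is no loss.

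The sizes rest on assumed stratum sizes, an assumed variance share, a residual SD of 3% and a two-sided 5% test. With the forced pairs included, the net direction of the error is not established. That the paired stores share an arm is itself an inference from the word *forced*. This is worth correcting because it is cheap, but it does not threaten the trial's validity.

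**What to change.** Restate the main model as: log 2023 outcome = arm + log 2021 baseline + randomisation stratum (the six partner store groups), and use the same form for the secondary purchasing outcomes. The investigators know the stratum sizes, so they can decide now whether the stratum enters as a fixed or a random effect and write that down; a stratum with stores in only one arm adds nothing to the contrast under fixed effects.

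In the same sentence, state how the two forced same-community pairs are handled: for example, analyse each pair as one community unit (pooling its sales before forming the ratio), or include a community-level cluster term. With only two pairs, a community variance would be poorly estimated, so the single unit is the simpler option. It leaves 32 − 2 = 30 units if no other stores share a community. Also state which arm each pair was in.

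The cost is a few lines of wording and no new data. Statistically it is up to 5 degrees of freedom: about 1 point of power if partner group carries no information, possibly 2 to 3 if strata are very uneven. Treating pairs as units removes two observations. The change should be recorded before the blinded analysts see results by arm. If the omission is deliberate, the reason should be stated.

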**Discussion:**

We hypothesise that the benchmarking intervention can improve the adoption of health-enabling store policy and practice and reduce sales of unhealthy foods and drinks in remote community stores of Australia. This innovative research with remote Aboriginal and Torres Strait Islander communities can inform effective implementation strategies for healthy food retail more broadly.

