Benchmarking with continuous improvement therefore provides a potential strategy to strengthen health-enabling best-practice adoption by remote community store directors/owners. The goal of the research reported herein is to co-design a model to facilitate benchmarking in the remote store setting, and test its effectiveness. We hypothesise that a codesigned benchmarking intervention can improve the adoption of health-enabling store policy and practice and reduce sales of unhealthy foods and drinks and therefore free sugars to energy purchased, in remote community stores of Australia.

This paper outlines the study protocol for the Benchmarking for Healthy Remote Aboriginal and Torres Strait Islander stores randomised controlled trial. An assessment of adoptability (including an economic evaluation) will be conducted and described separately to this paper. We use the SPIRIT 2013 Checklist: Recommended items to address in a clinical trial protocol and related documents, for this purpose, and report our research practice against The Aboriginal and Torres Strait Islander Quality Appraisal Tool designed by the Centre of Research Excellence in Aboriginal Chronic Disease Knowledge Translation and Exchange (hereafter the ‘CREATE Tool’) [42, 43]. Developers of this tool encourage its use in planning research ‘to achieve appropriate, high quality and relevant research that benefits Aboriginal and Torres Strait Islander peoples’ [43]. It emphasises the importance of Aboriginal and Torres Strait Islander leadership and partnership and is designed so that research effort reflects Aboriginal and Torres Strait Islander Peoples’ ways of knowing, being, and doing [43].

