**Fig. 3 Fig3:**
[figure not shown]
The benchmarking and continuous improvement cycle of assessment, feedback, action planning and implementation. Adapted from the PLAN-DO-COLLECT-LEARN cycle, Menzies School of Health Research [63]. This figure shows the four components of the cycle and the sharing of this information with store directors/owners as represented by the middle section of the figure. Artwork by Ngarrindjeri artist [name]

Control stores receive an in-store assessment of their best-practice implementation at one time each year for three years (2022, 2023, 2024) and provide weekly store sales data (52 weeks pre to 52 weeks post intervention). They are offered a full benchmarking cycle in 2024, prior to which they will continue with usual retail practice.

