#### Outcomes

Primary outcome: Change in the last six-months (July-December 2023) from baseline (July-December 2021) in free sugars from all food and drinks purchased (g sugar/MJ total energy), derived from electronic point-of-sale data.

Secondary outcomes: Change from baseline to i) last six months of 2022 and ii) last six-months of 2023 for the following purchasing outcomes derived from data of all food and drinks purchased:free sugars (g/MJ total energy)discretionary products weight (g/MJ total energy)core products weight purchased (g/MJ total energy)sodium (mg/MJ total energy)

Change from baseline (2022) in 2023 and 2024 in adoption of best-practice store policy action and practice implementation.

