#### Participant timeline

For intervention stores, the benchmarking cycle involves an assessment in July/August of 2022, 2023 and 2024. Feedback reports are then provided to partners for store groups and independent stores directly between October/November of 2022, 2023 and 2024. Action plan meetings are arranged by partners with stores following receipt of feedback reports in 2022 and 2023. Store directors/owners/ management then have responsibility to implement the co-designed action plans. Action implementation occurs following action plan meetings to June of each year before assessment starts again in July/August.

For control stores, data collection occurs in July/August, 2022 (using Store Scout App) and 2023 (using Store Scout App and Healthy Diets ASAP). One full benchmarking cycle will be completed, commencing with assessment in July/August, 2024.

As shown in Table 1, weekly sales data are collected from intervention and control stores from 2021 to 2025.

**Table 1 Tab1:** Summarised benchmarking performance metrics and data collection methods

Benchmark assessment area	Stores assessed	Data collector	Data collection instrument (Supplementary material)	Estimated data collection time
i) Policy: adoption of health-enabling best-practice store policy	Intervention stores (2022, 2023, 2024) Control stores in 2024	Store owner/s (for privately owned stores), store representatives or store nutritionists for stores with ALPA or Outback Stores (and with area managers for Outback Stores)	Policy Action Progress Audit e-survey: 24 three-part item survey on adoption status (full, partial, getting started, not yet started) of 21 industry- and research-informed policy actions [62]. Survey informed by research evidence, the remote food retail, government policy and health and research sectors, and BIA-Obesity, and built in REDCap [32, 64].	~ 30 min
ii) Practice: implementation of best-practice	Intervention and control stores (2022, 2023, 2024)	Trained partner nutrition practitioners/research team	Store Scout App [65]: 293 item survey on product, placement, price promotion, and product promotion in seven food/drink categories [59].	40-60 min
iii) Price: Price of standardised healthy diet	Intervention and control stores (2023/2024 only)	Trained partner nutrition practitioners/research team	Aboriginal and Torres Strait Islander Healthy Diets ASAP: on-line survey to collect food price data on 76 healthy and unhealthy food/ drink products [61].	~ 60 min

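### The Store Scout practice score, a hypothesised secondary outcome measured in both arms in all three years, is planned for description only, with no baseline-adjusted between-arm estimate or confidence interval

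*Protocol article*

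**What the plan says.** - **Hypothesis.** The Background states: "We hypothesise that a codesigned benchmarking intervention can improve the adoption of health-enabling store policy and practice and reduce sales of unhealthy foods and drinks". The Abstract's discussion paragraph repeats it: "We hypothesise that the benchmarking intervention can improve the adoption of health-enabling store policy and practice".
- **Outcome.** The Outcomes section lists as secondary: "Change from baseline (2022) in 2023 and 2024 in adoption of best-practice store policy action and practice implementation".
- **Measurement.** The Practice row of Table 1 gives the stores assessed as "Intervention and control stores (2022, 2023, 2024". The Intervention section agrees: "Control stores receive an in-store assessment of their best-practice implementation at one time each year for three years (2022, 2023, 2024".
- **Scale.** The practice assessment paragraph says: "An overall score out of 100 is derived automatically by the Store Scout App following each store assessment in 2022, 2023 and 2024". Each food/drink category is also scored out of 100.
- **Timing.** The Participant timeline places assessments in July/August and feedback reports in October/November. For control stores it adds: "One full benchmarking cycle will be completed, commencing with assessment in July/August, 2024".
- **Analysis.** The practice assessment paragraph says: "Differences in total and category scores with time for intervention stores and between intervention and control stores will be described". Earlier in the same section, change over time in policy and practice is to be described and used to interpret the other outcomes. The only model named in the article is an ANCOVA on sales data.

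**The concern.** The outcome is defined as change from a 2022 baseline, and the trial is randomised. The quantity these two facts imply is the between-arm difference in practice, given the 2022 score. The analysis text does not specify it. It offers change over time within intervention stores, which does not use the randomisation, and a difference between arms with no stated baseline adjustment or interval.

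This matters because the article attributes the expected 3.5% fall in free sugars to changed retail practice and intends to use the practice results to interpret the sales results. If sales do not move, the reader will ask whether practice moved. A bare difference between two small groups of stores gives little basis for an answer. The policy audit cannot take its place, because Table 1 has control stores completing it in 2024 only. Of the two adoption measures, practice is therefore the only one with a randomised comparison of change.

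**Working it through.** **Does the design support an adjusted comparison?**

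1. Baseline: the 2022 assessment (July/August) precedes the first feedback (October/November), in both arms.
2. Follow-up in 2023: control stores have had assessment only.
3. Follow-up in 2024: the control assessment is the first step of the control stores' own cycle, so it precedes their feedback and action plan.

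Both follow-up contrasts therefore come before any control-store feedback.

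**What precision could be expected?** The article gives no figure for the practice score; its sample size concerns free sugars only. The inputs are:

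- Stores: 15 intervention and 17 control (Allocation).
- SD of the score across stores: assumed 5, 10 or 15 points.
- Correlation r between the 2022 score and follow-up: assumed 0, 0.5 or 0.7.

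The half-width of the 95% interval from an ANCOVA on arm and baseline, with 32 − 3 = 29 degrees of freedom, is

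t(0.975, 29) × SD × √(1 − r²) × √(1/15 + 1/17) = 2.045 × SD × √(1 − r²) × 0.354.

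| SD | r = 0 | r = 0.5 | r = 0.7 |
|---|---|---|---|
| 5 | 3.6 | 3.1 | 2.6 |
| 10 | 7.2 | 6.3 | 5.2 |
| 15 | 10.9 | 9.4 | 7.8 |

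**Chance baseline imbalance.** The standard error of the difference in mean 2022 scores is SD × 0.354, which is 1.8, 3.5 and 5.3 points at SD 5, 10 and 15. An unadjusted follow-up difference carries r times whatever imbalance occurs.

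**Adjusted score against change score.** At SD 10 and r = 0.6:

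- ANCOVA: 2.045 × 10 × √(1 − 0.36) × 0.354 = 5.8.
- Change score: 2.042 × 10 × √(2 × (1 − 0.6)) × 0.354 = 6.5.

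The gain is real but modest.

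**Stratum terms.** Six partner groups take 5 more degrees of freedom and leave 24. Then t = 2.064 instead of 2.045, about 1% wider before any variance that the strata explain and any arm imbalance within strata.

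**Same-community pairs.** The Allocation section names two pairs of stores whose allocation was forced. If each pair is averaged, 30 units remain. The article does not say which arm the pairs are in. With splits of 15/15, 14/16 or 13/17 and stratum terms (22 degrees of freedom, t = 2.074), the half-widths are about 5% wider than in the table, if an averaged pair is taken to be no more precise than a single store.

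**Power.** Without baseline adjustment, a two-sample t-test with 15 and 17 stores detects about 1.03 SD at 80% power and 1.19 SD at 90%.

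**The case against.** **A between-arm difference is already planned.** This stands. A described difference in a 0-100 score is a point estimate. A reader might infer that practice gets no effect estimate at all, and the quoted sentence does not support that. Nor does the word described rule out an interval; none is specified.

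**Such detail belongs in the statistical analysis plan.** This stands in part. That plan is not shown and could add a model. But the article does not leave the method open: it says twice that practice results will be described, while naming a model for sales.

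**Description is a coherent choice for an unpowered measure in 32 stores.** The trial is sized on free sugars only, and a difference of about 1 SD would be needed for 80% power. That is a good reason to make no power claim. It does not justify omitting the interval, which is what shows how little or how much the data can exclude.

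**The contrast is not free of bias.** This stands. One might infer from the timing that the randomised comparison is clean. It is clean only of control-store feedback. Table 1 has the score collected by partner nutrition practitioners or the research team, partner practitioners also deliver the intervention, and the Blinding section says data collectors are not blinded. Allocation was within partner groups, so the same organisations serve both arms. Baseline adjustment removes neither detection bias nor contamination.

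**Conclusion.** The point holds in a limited form. Practice implementation is hypothesised, is listed as a secondary outcome defined by change from 2022, and is scored in both arms in all three years. Its planned analysis is descriptive, with no baseline-adjusted between-arm estimate or confidence interval specified. This is a weakness in how the article fixes a secondary analysis. It is not a contradiction and does not touch the primary outcome.

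The size rests on assumptions, since the documents give no SD or correlation for the score. The 95% half-width would be about 2.6 to 10.9 points for SDs of 5 to 15 and correlations of 0.7 to 0, and somewhat wider once partner group and the store pairs are allowed for. A reader might expect the adjusted estimate to settle whether practice changed. With this precision and unblinded scoring it may not, but it would show what the data can and cannot exclude.

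**What to change.** For the total Store Scout score, replace the descriptive plan with the between-arm difference in 2023 and in 2024, each with a 95% interval, from an ANCOVA on arm, 2022 score and randomisation stratum (partner group). Allow for the two same-community pairs, for example by averaging each pair. Keep the category scores descriptive. Present the result as a secondary estimate without a power claim. State as a limitation that scoring is unblinded and partly done by practitioners who deliver the intervention.

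The cost is a short change of text and two extra model fits on data already planned in both arms. The downside is modest precision.
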